### Statistical analyses

Descriptive statistics will be calculated for demographic and potential confounding variables (i.e., injury type, time since injury, prior or subsequent injury, prior treatment), and observed differences will be considered when interpreting findings, and during the design of a future hybrid effectiveness-implementation RCT. Randomization integrity will be monitored. Mean changes in all outcomes between T0 and T1, and T1 and T2 will be described by study group and sex (knee extension torque) or gender (physical activity, KOOS, KSES).

We will conduct intent-to-treat analyses (compare outcomes according to randomized study groups, regardless of intervention adherence). Missing outcome data due to missed visits or dropouts will be handled using multiple imputations of missing values. Generalized linear mixed-effects regression models for longitudinal data (95%CI), controlling for blocking effect, will estimate the effect of the 8-week intervention (IG T1-T0 versus DG T1-T0, and DG T2-T1 versus T1-T0) and delay (IG T1-T0 versus DG T2-T1) for the primary outcome (knee extension torque change; Fig. 3).

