### Procedures

Figure 1 outlines the study phases for participants with a past knee injury. Interested persons will be directed to an online screening survey (Qualtrics XM, US) and those potentially eligible will be emailed study information and scheduled for a videoconferencing interview to confirm eligibility. Eligible persons will receive an URL to an electronic consent form located on a data management platform (REDCap 10.9.4, Vanderbilt University, US). After consenting, participants will complete baseline testing and be randomly allocated to study group (see below). The immediate study group (IG) will be complete an 8-week (weeks 1–8) SOAR program (Knee Camp, home-based exercise-therapy and physical activity with tracking, weekly 1:1 PT counseling sessions, and optional weekly group-based exercise classes) followed by an additional 8 weeks (weeks 10–17) of home-based exercise-therapy and physical activity with tracking, weekly 1:1 PT counseling sessions, and optional weekly group-based exercise classes. In contrast, after a 10-week delay, the delayed study group (DG) will complete an 8-week (weeks 10–17) SOAR program (Knee Camp, home-based exercise-therapy and physical activity with tracking, weekly 1:1 PT counseling sessions, and optional weekly group-based exercise classes). Knee injury participant outcomes will be evaluated at baseline (T0), 9-weeks (T1-primary endpoint to assess efficacy), and 18-weeks (T2- endpoint to inform optimal intervention length).

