### Randomization allocation, concealment and blinding

After baseline testing, knee injured participants will be randomly assigned to IG or 10-week DG groups in a 1:1 allocation ratio, stratified on sex in variable block sizes [4, 6, 8]. A research coordinator will use serial labelled opaque envelopes prepared by a statistician (blind to data collection and daily trial activities) with a randomization schedule (SAS v9.4) to reveal group assignment.

The nature of the intervention does not allow for full blinding (i.e., participants and PTs cannot be blinded to study group). To reduce allocation bias, participants will be randomized to study groups by a research coordinator using serial labelled opaque envelopes prepared by our statistician (no interaction with participants and blind to data collection and daily trial activities). To reduce confirmation bias, persons leading outcome assessment and analyses will be blinded to group allocation, and participants will be asked not to disclose allocation to assessors. All questionnaires are self-reported (assessor blinded). Participants will also be blinded to study hypotheses.

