#### Participant characteristics

Age, gender (woman, man, gender-diverse, trans-gender, other), sex (female, male, intersex), ethnicity, current employment status, education attained, sport participation (main pre-injury sport, return-to-sport, participation in last year), and injury history (injury age, injury type, time since injury, treatment received, subsequent injury) will be collected with a baseline questionnaire. Participants were asked to answer all questions in reference to the study knee injury, or in the case of bilateral knee injuries, the most symptomatic.

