**Fig. 3 Fig3:**
[figure not shown]
Analysis contrasts

We will conduct three exploratory analyses to guide design of the future hybrid effectiveness-implementation RCT. To inform primary outcome choice individual generalized linear mixed-effects regression models for longitudinal data (95%CI), controlled for blocking effect, will explore the effect of the 8-week program (IG T1-T0 versus DG T1-T0) on MVPA time, KOOS function in sport/recreation sub-scale, and KSES considering gender. To inform the most relevant muscle function outcome individual linear regression (95%CI) models, adjusted for age and sex, will compare the association between the change in knee extensor muscle function torque, power, and rate of force development over the 8-week intervention with the KOOS_4_. To inform optimal intervention length, a longitudinal mixed-effects model will examine the intervention effect at 18-weeks. This model will include the following fixed effects indicators: 1) study group (i.e., IG or DG) to account for baseline difference; 2) follow-up point (i.e., T1 or T2) to account for secular trend, and; 3) time since intervention initiation (i.e., 18- or 9-weeks) to estimate effects after these time intervals. The model will also include participant-specific random effects to account for repeated measures. As type II error is a greater concern in proof-of-concept trials than type I, we will not adjust for multiple comparisons [81].

Interview recordings will be transcribed verbatim and de-identified. Using a constant comparative approach [77] data will be coded and categories developed by comparing and determining meaningful patterns across codes. High-order themes will illuminate the relationship between categories. We will look for uniqueness in experience by gender. If gender-based themes are identified, data will be reanalyzed with a gender lens. Analysis credibility and trustworthiness will be fostered through data immersion, reflexive journaling, field notes, memoing and regular research team discussions of coding, early concepts and developing themes. A detailed audit of analytic decisions will be kept [82].

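### The primary torque contrast is a difference in change that makes no stated use of pre-randomisation torque; a common-baseline model would gain precision at no cost

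*Protocol article*

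**What the plan says.** The Statistical analyses section plans "Generalized linear mixed-effects regression models for longitudinal data (95%CI), controlling for blocking effect". The effect of the 8-week programme is written as "IG T1-T0 versus DG T1-T0, and DG T2-T1 versus T1-T0", together with a contrast for delay (IG T1-T0 against DG T2-T1), all "for the primary outcome (knee extension torque change; Fig. 3"). The blocking effect is the only adjustment named. The text does not say whether the response is a computed change or the repeated torque values, nor whether the two groups share a baseline mean.

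Under Randomization allocation, concealment and blinding, allocation follows baseline testing and is "stratified on sex in variable block sizes" of 4, 6 and 8. Sex enters the primary analysis section only as a way of describing mean torque changes.

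The text after Fig. 3 gives the exploratory models. Those for MVPA, KOOS sport/recreation and KSES use the same IG-versus-DG contrast, control for blocking and consider gender. The muscle-function models adjust for age and sex. The 18-week model has a term for "study group (i.e., IG or DG) to account for baseline difference".

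**The concern.** T0 torque is measured before allocation, so the two groups have the same expected baseline. A comparison of T1-T0 changes does not use that fact. It subtracts the whole baseline value, noise included, where the data would support subtracting only the part that predicts T1. A longitudinal model with a separate baseline mean for each group gives the same T1-T0 contrast when data are complete, so calling the model longitudinal does not by itself recover the precision. A common baseline mean, or baseline torque as a covariate, does; in large samples neither is less precise than the change comparison.

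What is at stake is the width of the confidence interval and the power. The protocol treats type II error as the greater worry in a proof-of-concept trial and gives that as its reason for not adjusting for multiplicity. Baseline adjustment lowers type II error without raising type I error. The sample size covers torque only, so the exploratory models with the same contrast have no stated power at all.

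**Working it through.** **Inputs from the Sample size section.** Difference 0.22 Nm/kg; SD 0.25 Nm/kg; two-sided alpha 0.05; power 80%; 21 per group; 70 recruited with 25% attrition allowed. The article does not say whether 0.25 is the SD of change or of a single measurement.

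**Assumed input.** The T0-T1 correlation r of torque is not given. The range used is 0.6 to 0.9, with equal variances at T0 and T1.

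**1. The plan's own figure.** n per arm = 2 × (1.96 + 0.8416)² × 0.25² / 0.22² = 20.3, rounded up to 21, or 42 in total. The stated figure reproduces. The noncentral t distribution gives 79.5% power at 21 per arm.

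**2. Variance ratio.** With single-visit variance s² and n per arm:
- change contrast: 2s²(1−r) × 2/n
- baseline-adjusted contrast: s²(1−r²) × 2/n
- ratio: (1−r²) / [2(1−r)] = (1+r)/2
- equivalent gain in participants: 2/(1+r) − 1

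**3. Power, taking 0.25 as the SD of change.** The adjusted SD is 0.25 × √((1+r)/2). Power is from the noncentral t, with one degree of freedom spent on baseline. Retention of 75% of 70 is 52.5, taken as 26 per arm.

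| r | Ratio | Equivalent extra participants | Adjusted SD | Needed per arm | Power at 21 per arm | Power at 26 per arm |
|---|---|---|---|---|---|---|
| change score | 1 | none | 0.250 | 21 | 79.5% | 87.5% |
| 0.6 | 0.80 | 25% | 0.224 | 17 | 87.5% | 93.5% |
| 0.8 | 0.90 | 11% | 0.237 | 19 | 83.4% | 90.6% |
| 0.9 | 0.95 | 5% | 0.244 | 20 | 81.4% | 89.1% |

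If all 35 per arm were evaluable, the change comparison alone would have about 95% power.

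**4. If 0.25 is a single-measurement SD.** The SD of change is then 0.25 × √(2(1−r)). The ratio is unchanged, but power is higher under both analyses: at 21 per arm, 87.5% against 93.5% at r = 0.6, and 99.3% against 99.6% at r = 0.8.

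**5. Where the gain comes from.** A simulation of 70 participants (1,500 replicates; 35 per sex; blocks of 4, 6 and 8 within sex; SD of change 0.25; an assumed sex difference of 0.4 Nm/kg in level) gave these standard errors for the group effect:

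| Model | r = 0.6 | r = 0.8 | r = 0.9 |
|---|---|---|---|
| change only | 0.0582 | 0.0604 | 0.0606 |
| change + sex | 0.0582 | 0.0605 | 0.0607 |
| change + block | 0.0588 | 0.0614 | 0.0609 |
| baseline-adjusted | 0.0531 | 0.0585 | 0.0596 |
| baseline + sex | 0.0524 | 0.0586 | 0.0596 |
| baseline + block | 0.0530 | 0.0595 | 0.0599 |

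Simulation error is about 0.06/√(2 × 1,500) = 0.001 per entry; all models were fitted to the same simulated data sets. Nearly all of the gain comes from baseline torque. Sex adds little or nothing, and block indicators cost less than 2% (0.0604 to 0.0614 at r = 0.8).

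**The case against.** The strongest reply is that the article does not commit to raw change scores. A T1-T0 comparison between groups is how a group-by-visit contrast is written in any longitudinal model, including one with a common baseline. The wording about accounting for a baseline difference belongs to the exploratory 18-week model. How baseline enters is often left to an analysis plan, and none is shown here. This stands in part: the loss is conditional on baseline means being left free. But the article does fix the contrast and does name its adjustment, and on the usual reading those give the change comparison.

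A second reply also stands. Regressing T1 on T0 torque cannot produce the contrasts that use T2, so one longitudinal model over all three visits is a sensible choice. The remedy should keep it.

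Three stronger readings are tempting and are not supported:
- **That sex is left uncontrolled.** Blocks are formed within sex strata, so terms for block already absorb sex.
- **That block terms waste material precision.** About 12 blocks (70/6) as fixed effects would use about 11 degrees of freedom, but the article does not say they are fixed. Even if they are, going from about 50 to 39 degrees of freedom moves the critical t only from 2.01 to 2.02, and the simulated standard error rises by under 2%.
- **That gender replaces the stratification factor in the other models.** Those models keep the blocking control and add gender. They are labelled exploratory, and their KOOS outcome is sport/recreation, not quality of life.

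**Conclusion.** The point holds as a matter of efficiency. As written, the primary contrast makes no stated use of the pre-randomisation torque value. Unless the baseline means are constrained equal, its variance is larger than it need be: the adjusted variance would be 0.80 to 0.95 of it for r between 0.6 and 0.9. In power at 21 per arm, that is a gain of about 8 points at r = 0.6, 4 at r = 0.8 and 2 at r = 0.9. These figures rest on equal variances at T0 and T1, on 0.25 Nm/kg being the SD of change, and on an r that the article does not supply.

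A reader might infer that the primary result would be biased by baseline imbalance or regression to the mean. It would not: under randomisation the change comparison is unbiased, and chance imbalance matters only conditionally on the sample drawn. Nor is the primary test at risk, since the change comparison has about 87.5% power at 26 per arm on the plan's own inputs. The undefined blocking term is a smaller matter of clarity.

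**What to change.** Keep the single mixed model for torque at T0, T1 and T2, and state four things:

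1. The T0 mean is constrained equal in the two groups, with group effects free at T1 and T2, and the primary effect is the IG-minus-DG difference at T1. All the planned contrasts remain available. Baseline torque as a covariate is an acceptable alternative for the T1 contrast alone.
2. Sex, as the randomisation stratum, is an explicit term.
3. What the blocking effect is: the sex stratum, or the individual blocks, and if the blocks, whether fixed or random.
4. The exploratory MVPA, KOOS sport/recreation and KSES models handle baseline in the same way, with gender considered in addition as already planned.

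The cost is a few sentences of analysis wording, settled before unblinded data are seen. Baseline torque and sex are already collected, and the sample size and visits do not change.

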### Data collection and management

Data will be obtained through questionnaires hosted on a secure online survey platform (REDCap 10.9.4, Vanderbilt University, US). At each testing period knee injury participants will also attend a 1-h in-person laboratory session to complete computerized dynamometry testing of knee extensor and flexor muscle function, and a dual x-ray absorptiometry scan to estimate body mass index and body composition. At the end of the in-person session, participants will be given a triaxial accelerometer and instructed on how to wear it for 7-days. The accelerometer will be returned in a postage paid courier envelope. Secure online forms (Microsoft© Sharepoint) will be used to track knee injury participants attendance, adverse events, healthcare use, exercise/activity goal completion, Rating of Perceived Effort, and any associated pain. Data will be stored in secure electronic databases and de-identified. All authors will have access to the final dataset.

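### The planned delay contrast (IG T1-T0 versus DG T2-T1) mixes any delay effect with the difference in no-programme change between two periods, and the design cannot separate them

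*Protocol article*

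**What the plan says.** The Statistical analyses section gives the primary outcome, change in knee extension torque, a generalized linear mixed model with 95% confidence intervals. The only adjustment it names is for blocking. For the programme itself, the model "will estimate the effect of the 8-week intervention (IG T1-T0 versus DG T1-T0, and DG T2-T1 versus T1-T0", the second of these being a comparison within the delayed group (DG). The same sentence then adds a third comparison under a different label: "and delay (IG T1-T0 versus DG T2-T1) for the primary outcome".

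Procedures sets the timing. Tests take place at baseline (T0), 9 weeks (T1) and 18 weeks (T2). After its first course the immediate group (IG) goes on: "followed by an additional 8 weeks (weeks 10–17) of home-based exercise-therapy and physical activity with tracking", with weekly counselling and optional classes. After the wait, "the delayed study group (DG) will complete an 8-week (weeks 10–17) SOAR program". Data collection and management has everyone repeat the strength test: "At each testing period knee injury participants will also attend a 1-h in-person laboratory session to complete computerized dynamometry testing".

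The only time term named in Statistical analyses belongs to a separate exploratory model for intervention length, which includes "follow-up point (i.e., T1 or T2) to account for secular trend".

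**The concern.** Randomisation makes the two groups comparable. It does not make weeks 0-9 comparable with weeks 9-18, or a first-to-second test comparable with a second-to-third. Strength scores can change without the programme, through familiarity with the dynamometer, continuing recovery or a secular trend. If that change differs between the two periods, the difference passes straight into the figure labelled delay.

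What is at stake is what the trial may say about delay. A familiarisation gain confined to the first retest would make an immediate start look better than a delayed start when delay has no effect. A null could equally be a real delay effect cancelled by unequal change.

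**Working it through.** **The plan's own figure.** The protocol gives no number for the delay contrast. Its sample size, from a difference of 0.22 Nm/kg, SD 0.25, two-sided α 0.05 and power 0.80 (Sample size), reproduces:

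n per group = 2 × (1.960 + 0.842)² × 0.25² / 0.22² ≈ 20.3, rounded up to 21, so 42 in total.

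**Expected means.** Let a and b be the baseline means. Let s1 and s2 be the no-programme changes from T0 to T1 and from T1 to T2. Let E_IG and E_DG be the effects of a first course in each group, and E18 the IG effect at 18 weeks.

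| | T0 | T1 | T2 |
|---|---|---|---|
| IG | a | a + s1 + E_IG | a + s1 + s2 + E18 |
| DG | b | b + s1 | b + s1 + s2 + E_DG |

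**Contrasts.**

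- IG T1-T0 minus DG T1-T0 = (s1 + E_IG) − s1 = E_IG. It is clean.
- IG T1-T0 minus DG T2-T1 = (s1 + E_IG) − (s2 + E_DG) = (E_IG − E_DG) + (s1 − s2). This is the delay effect plus the difference in no-programme change.

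**Can the two parts be separated?** DG T1-T0 shows s1. But s2 appears only in the T2 means, and there always beside a programme effect (E18 in IG, E_DG in DG). The model has seven parameters and six cell means, with rank 6, and E_IG − E_DG is not estimable. Setting a = b does not help (six parameters, rank 5). The delay effect becomes estimable only if s1 = s2 is assumed or s2 is fixed from outside the trial.

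**The intervention-length model.** It uses one 9-week effect for both groups, that is, E_IG = E_DG. That leaves six parameters on six cells (rank 6), so the trend can be estimated, but only by assuming that delay has no effect. It cannot be used to correct the delay contrast.

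**Size.** The documents give no value for s1 − s2, so the values here are assumptions.

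- As a share of the target: 0.03/0.22 = 14% and 0.07/0.22 = 32%.
- As false findings, with E_IG = E_DG and 0.25 taken as the SD of change: SE = 0.25 × √(2/n), which is 0.077 at 21 per group and 0.060 at 35. With D = s1 − s2, the chance that the 95% interval excludes zero is Φ(−1.96 + D/SE) + Φ(−1.96 − D/SE).

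| Assumed D (Nm/kg) | 21 per group | 35 per group |
|---|---|---|
| 0 | 5.0% | 5.0% |
| 0.02 | 5.8% | 6.3% |
| 0.05 | 9.9% | 13.3% |
| 0.08 | 17.9% | 26.8% |
| 0.11 | 29.7% | 45.3% |

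A larger sample makes this worse, because the displacement stays while the interval narrows.

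**One alternative case.** If s2 = 0, subtracting DG T1-T0 from the planned contrast removes s1: (IG T1-T0) − (DG T2-T1) − (DG T1-T0) = IG T1-T0 versus DG T2-T0, with expectation E_IG − E_DG.

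**The case against.** The strongest reply is about consequence. Delay is not among the objectives in Aim, is not mentioned as a question in the abstract, and is not one of the three exploratory analyses meant to guide the future trial. A reader might infer that a misleading delay result would steer that trial, or that a null would be taken as proof that waiting is harmless. The documents state no decision that depends on delay, so neither inference is supported. This stands and limits the weight of the point.

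A reader might also infer that the efficacy result is biased. It is not: IG versus DG, both T1-T0, is concurrent and randomised. The within-group comparison DG T2-T1 versus T1-T0 has the same weakness (expectation E_DG + s2 − s1), but it has that randomised contrast beside it. The delay contrast has no such counterpart.

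It is tempting to say that the protocol adjusts for trend in one model and forgets to in the other. That goes too far. The intervention-length model answers a different question and offers no adjustment that could have been borrowed.

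The other replies:

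- Sample size assumes no change in the delayed group. That is a planning input for the first period. With s1 = 0 the contrast is still displaced by −s2, which is not observed.
- Mean changes for T0-T1 and T1-T2 will be described by group, so a reader will see s1. That is true and makes the fix cheap, but it does not reveal s2.
- Staggered entry may average out season. It cannot average out test order, which is fixed within every participant.
- Therapists with more experience by the second period would alter E_DG, which is arguably part of starting later. It is not counted here as bias.
- An unseen analysis plan might add terms. No covariate identifies the effect; only an assumption does.

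**Conclusion.** The point holds for the delay contrast alone. As written, the protocol promises an estimate of delay that the design can deliver only if no-programme change is equal in both periods, and Statistical analyses neither states nor justifies that assumption.

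The identification result rests only on the visit schedule, the repeated testing and the absence of an untreated arm in weeks 10-17. The size is not known. The 14-32% of target and the false-finding rates depend on assumed differences and on reading 0.25 Nm/kg as the SD of change; they are illustrations. If the two no-programme changes happen to be equal, the contrast is unbiased, but the trial's data cannot show that they are.

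**What to change.** In Statistical analyses, stop calling IG T1-T0 versus DG T2-T1 an estimate of the effect of delay. Call it a descriptive comparison of first-course gains, and state that it equals a delay effect only if no-programme change is the same in both periods.

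Report beside it the version that assumes no such change in the second period, IG T1-T0 versus DG T2-T0. Present the two as a sensitivity range. They are not bounds, because season or recovery could make s2 larger than s1 or opposite in sign, so agreement between them should not serve as a decision rule. Add that neither a difference nor a null establishes or excludes a delay effect.

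This needs wording and one further linear combination of means already in the model, with no new data. The cost is a weaker claim about delay.
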